## Abstract

**Background:**

During follow-up of glioblastoma patients after chemoradiation, expert teams often observe abnormalities on MRI with difficulty in distinguishing between tumor growth and pseudoprogression. Although advanced MRI techniques such as perfusion weighted imaging provide additional information, diagnostic uncertainty often remains, leading to incorrect or delayed diagnosis, and inappropriate treatment, such as unnecessary surgery. [^18^F]Fluoro-ethyl-tyrosine positron emission tomography (FET PET) has good discriminating power for this setting. Still, this diagnostic tool is not used frequently in The Netherlands due to costs, logistics and uncertainty about clinical benefit. In the FET POPPING study, we aim to determine the added value of [^18^F]FET PET for clinical management of glioblastoma patients.

**Methods:**

A multicenter diagnostic randomized clinical trial will be performed, from August 2024 until December 2027. Adult patients (*n*=144) with isocitrate dehydrogenase (IDH)-wildtype glioblastoma will be included, who, at least ≥3 months after the concomitant phase of standard temozolomide-based chemoradiation, have new or increased contrast enhancement on MRI, causing doubt between tumor growth or pseudoprogression.

In this trial, pseudoprogression will be used as an encompassing term that includes radionecrosis and other treatment-related changes after (chemo-)radiotherapy. Included patients will be randomized 1:1 in two arms. The investigational arm receives an additional [^18^F]FET PET scan, and clinical management is based on the index MRI and [^18^F]FET PET together. Clinical management of the control arm is based on the index MRI alone. Exact clinical management, as based on the available imaging, is chosen at the discretion of the local multidisciplinary board. The primary study endpoints are (a) the percentage of patients undergoing unnecessary interventions and (b) health-related quality of life after 12 weeks. Secondary endpoints include time-to-diagnosis, overall survival, and cost-effectiveness.

**Discussion:**

We hypothesize that the clinical management guided by an additional [^18^F]FET PET scan leads to fewer unnecessary interventions, better health-related quality of life after 12 weeks and among others reduced net healthcare costs, compared with management based on MRI only.

**Trial registration:**

The trial is registered on ClinicalTrials.gov on the 24th of June 2024, with registration number NCT06480721.

## Introduction

### Background and rationale {6a}

Glioblastomas are incurable progressive brain tumors with a variable, but poor prognosis. After surgery, chemoradiation with concomitant and adjuvant temozolomide chemotherapy offers effective, albeit temporary, palliation for many patients, with median overall survival of 14–16 months [1, 2]. In the months following radiotherapy, ~ 50% of patients will develop changes on MRI, suggestive of recurrence. In a majority of these patients, these MRI changes are classified as pseudoprogression [3]. Pseudoprogression is defined as treatment-induced increasing, or new, contrast enhancement which is mostly self-limiting and requires a different management strategy than tumor recurrence. Pseudoprogression will be used in this paper as an encompassing term that includes radionecrosis and other treatment-related effects after (chemo-)radiotherapy. Discrimination between pseudoprogression and tumor progression on MRI can be notoriously challenging [4]. In the patients that are eventually diagnosed with pseudoprogression, initial diagnostic uncertainty is common, which may lead to an increased risk of misdiagnoses and unnecessary interventions [5, 6].

Currently, in the Netherlands, in these patients with diagnostic uncertainty on MRI, the multidisciplinary team prefers to wait for a next scan in 6–12 weeks’ time for definitive diagnosis, leading to potential delay of diagnosis and adequate management and causing psychological burden for patients and their relatives with impact on quality of life [7].

The use of positron emission tomography (PET) with the radioligand [^18^F]Fluoro-ethyl-tyrosine, or [^18^F]FET PET in short, has the potential to differentiate treatment-related changes from tumor recurrence with higher accuracy compared to current clinical standard MRI including perfusion-weighted MRI [8–10]. Meta-analyses of literature confirm that addition of [^18^F]FET PET to MRI has higher diagnostic accuracy for differentiation of pseudoprogression from tumor recurrence compared with MRI alone [11, 12]. Recent literature has led to evidence-based recommendations by the Response Assessment in Neuro-Oncology (RANO) working group to add [^18^F]FET PET imaging to MRI in cases with diagnostic uncertainty [13].

However, this advice is not based on prospective randomized patient benefit- or cost-effectiveness studies, as neither have been performed.

Many studies of diagnostic test accuracy are available, but demonstrating high diagnostic accuracy is not equivalent to proving added value in clinical practice; since a diagnostic study is only the starting point of a clinical trajectory, clinical utility of a diagnostic test is best demonstrated in the context of the appropriate clinical workflow. A second problem for implementation of [^18^F]FET PET is that imaging costs are perceived to be relatively high, at least higher than an MRI with perfusion and in the light of the expected prognosis [14]. In somewhat comparable clinical settings, studies demonstrate that the addition of [^18^F]FET PET imaging is cost-effective [15, 16]. However, no cost-effectiveness studies have been performed concerning the addition of [^18^F]FET PET imaging when there is diagnostic uncertainty about pseudoprogression *versus* tumor progression in glioblastoma patients after concomitant chemoradiation.

Moreover, in spite of the high diagnostic accuracy, opinions of treating physicians are divided. Besides, [^18^F]FET PET is not reimbursed in several countries. Consequently, this leads to a subset of centers offering [^18^F]FET PET, where the treating physicians have positive opinions about [^18^F]FET PET and where budget is available. Demonstrating benefit of early, consistent use of [^18^F]FET PET in terms of patient outcomes and cost-effectiveness is therefore crucial to justify and ensure widespread availability for all patients with glioblastomas. Therefore, we aim to conduct a nation-wide prospective, randomized clinical trial to assess patient benefit and health economic impact of management based on the addition of [^18^F]FET PET to MRI, compared to only use of MRI, in glioblastoma patients with diagnostic uncertainty about tumor recurrence *versus* pseudoprogression after concomitant chemoradiation. Clinical management will be based on the imaging findings in both groups and will follow regular clinical guidelines for the imaging-based diagnosis.

### Objectives {7}

#### Primary objectives

To determine, in glioblastoma patients with diagnostic uncertainty between pseudoprogression and tumor progression on a follow-up MRI after concomitant chemoradiation (“index MRI”), whether the clinical management guided by an additional [^18^F]FET PET scan leads to fewer unnecessary interventions and better health-related quality of life after 12 weeks, compared with management based on MRI only.

#### Secondary objectives

To determine, in glioblastoma patients with diagnostic uncertainty between pseudoprogression and tumor progression on a follow-up MRI after concomitant chemoradiation (“index MRI”), whether clinical management guided by an additional [^18^F]FET PET scan, when compared to management based on MRI only, leads to:Cost-effective interventionShorter time-to-diagnosis Changes in overall survival Lower number of unnecessary treatment cyclesImproved HRQOL over time (continuous measure), measured at t=6 weeks and t=6 months.

### Trial design {8}

This study is a prospective, national multicenter diagnostic randomized clinical trial, with a superiority design (lower proportion of unnecessary interventions and better HRQOL, compared with standard care). Patients that fulfill the inclusion criteria and who provide informed consent will be randomized in equal proportions between two arms (see Fig. 1):Arm A: investigational armAdditional [^18^F]FET PET scan, as soon as possible after the index MRIClinical management is based on the index MRI and additional [^18^F]FET PET togetherArm B: control armClinical management is based on the index MRI only (standard care)

**Fig. 1 Fig1:**
[figure not shown]
Study design flowchart. Potential number of patients, and number of patients meeting inclusion criteria, is based on real-life data from the included centers, very conservatively set at 50% of historical patient numbers 2019–2021. * Patients not receiving the intervention ([^18^F]FET PET) will be included in final analysis and not be replaced, according to an intention-to-treat design. Follow-up questionnaires will be administered if feasible. In this way, bias due to selective drop-out between arms will be avoided. ^#^Withdrawal of consent due to patient preference may occur, but is expected to be rare since patients have minimal extra burden during follow-up; transfer of care to a non-participating hospital is possible, but occurs only very infrequently in clinical practice. ^@^ The study features is a single-timepoint intervention (regular MRI, already available at baseline; versus [^18^F]FET PET), making discontinuation of the intervention during follow-up a non-relevant issue

## Methods: participants, interventions and outcomes

### Study setting {9}

Patients are enrolled in 6 academic medical centers and 2 non-academic neuro-oncological hospitals in the Netherlands.

### Eligibility criteria {10}

#### Inclusion criteria

Patients with a glioblastoma, IDH-wildtype, WHO grade 4 (according to WHO 2021 criteria), treated with standard-of-care temozolomide-based concomitant chemoradiation (60 Gy in 30 fractions or 40 Gy in 15 fractions) [17].Age ≥18 years.Follow-up MRI ≥ 3 months after the end of the temozolomide-based concomitant chemoradiation.New or increased enhancement within the high-dose radiation field (defined as within the 80% isodose line) on follow-up MRI.First moment of clinicoradiological uncertainty regarding the diagnosis (≥ 3 months after the end of concomitant chemoradiation): pseudoprogression or tumor progression. The determination of “uncertainty” is made by the treating physician, preferably in the multidisciplinary tumor board, based on available clinical and standard-of-care MRI-data, which generally includes perfusion-weighted MRI.Previous usage of bevacizumab as a symptom treatment is allowed. However, inclusion is only allowed at the first moment of clinical doubt between pseudoprogression and tumor progression, not at later timepoints.

#### Exclusion criteria

Previous treatment for recurrence of disease.Largest diameter of the enhancing lesion of less than 1 cm on the index MRI, usually measured in the axial plane.In the newest RANO PET-criteria, it is advised to use [^18^F]FET PET for increasing lesions only in cases with a minimum lesion size [18].Life expectancy of less than 6 months, determined by the treating physician.Contra-indications for PET (claustrophobia, inability to lay still).Women of childbearing potential without adequate contraception during randomization and possible [^18^F]FET PET scan.Any other concomitant disease that may influence PET imaging or clinical outcomes of this study. This includes but is not limited to cerebral inflammatory diseases and other cancers with brain- or leptomeningeal metastases.

### Who will take informed consent? {26a}

When patients fulfill the in- and exclusion criteria, they will be asked by the treating physician if they are willing to be informed about the study. Subsequently, study information will be provided to the patient. Patients are given a 48-h informed consent window. Patients will be asked for informed consent by an authorized researcher.

### Additional consent provisions for collection and use of participant data and biological specimens {26b}

In the patient information letter, patients are asked for consent to use their pseudonymized data, including data on clinically performed tissue analyses (if available), in future studies and share their pseudonymized data with other neuro-oncologic research centers.

No biological specimens will be collected for the purpose of this study.

## Interventions

### Explanation for the choice of comparators {6b}

Clinical management based on MRI only is chosen as comparator as this is standard-of-care according to current Dutch- and international guidelines [19].

### Intervention description {11a}

Patients in the investigational arm will undergo the extra [^18^F]FET PET scan, with use of the O-(2-^18^F-fluoroethyl)-L-tyrosine ([^18^F] FET) tracer. The tracer will be provided free of charge by Curium™ for a subset of the patients (based on logistical availability and scheduling per patient). For this study, Curium™ does not have a role in the design, execution, analysis, interpretation, manuscript writing and/or decision to publish.

[^18^F]FET PET scanning will be performed according to the joint European Association of Nuclear Medicine (EANM)/European Association of Neurooncology (EANO)/Response Assessment in Neurooncology (RANO) guideline [20]. In most patients, a static scan (20–40 min post-injection) will be performed. Patients will be asked for additional (opt-in) consent to undergo a dynamic [^18^F]FET PET scan. If the logistics of the research site allow for this scan, these patients will undergo dynamic scanning (continuous scanning 0–40 min post-injection). Interpretation will be done by a nuclear medicine physician from the local center according to current European guidelines [20]. Central review will be performed by a panel of nuclear medicine physicians from the study team, specialized in [^18^F] FET PET scans.

Patients are treated according to current standard-of-care that is determined by the treating physician/multidisciplinary team, but will be based on the diagnosis from the static [^18^F]FET PET findings:In case of [^18^F]FET PET-diagnosis of tumor recurrence: a change in treatment regime will be made. Redo-debulking will be done only for clinical indications, including mass reduction or cytoreduction.In case of [^18^F]FET PET-diagnosis of pseudoprogression, or equivocal results: the ongoing treatment or observation will be continued, with addition of steroids and/or bevacizumab if needed for symptom relief. Redo-debulking will only be done for the rare indication of refractory symptoms of mass effect due to pseudoprogression.

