### Outcomes {12}

#### Primary study outcomes

##### Co-primary outcome 1

Undergoing any unnecessary intervention(s), as defined below. Determination of this dichotomous outcome measure “unnecessary interventions” will be done retrospectively, by the researchers and the treating physician after 6-month follow-up.

An “unnecessary intervention” is defined as:Biopsy or debulking for diagnostic uncertainty and/or with pseudoprogression as the final pathological diagnosis.The administration of one or more cycles of (temozolomide) chemotherapy as continued treatment for presumed pseudoprogression, in cases where the final diagnosis is tumor progression. The final diagnosis is based on clinicoradiological- and/or histopathological evidence.Starting and/or altering chemotherapy for presumed tumor progression, in cases where the final diagnosis is pseudoprogression. The administration of one or more doses of bevacizumab for presumed pseudoprogression, in cases with a final diagnosis of tumor progression.

##### Co-primary outcome 2

Health-related quality of life (HRQOL) (continuous measure): the European Organization for Research and Treatment of Cancer Quality of Life Core Questionnaire (EORTC-QLQ-C30) + Brain Cancer Module (EORTC-QLQ-BN20) at *t* = 12 weeks, preferably completed before follow-up imaging is performed.

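### The surgery item of co-primary outcome 1 scores as unnecessary the one redo-debulking allowed after a pseudoprogression or equivocal PET reading, whenever pathology confirms pseudoprogression

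*Protocol article*

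**What the plan says.** **Care after PET (Intervention description {11a}).** A pseudoprogression reading and an equivocal one share a single instruction: "or equivocal results: the ongoing treatment or observation will be continued", with steroids or bevacizumab for symptoms where needed. On surgery the same bullet states: "Redo-debulking will only be done for the rare indication of refractory symptoms of mass effect due to pseudoprogression".

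**What counts (Outcomes {12}, co-primary outcome 1).** The surgery item reads: "Biopsy or debulking for diagnostic uncertainty and/or with pseudoprogression as the final pathological diagnosis". The continued-treatment item covers "chemotherapy as continued treatment for presumed pseudoprogression, in cases where the final diagnosis is tumor progression". The bevacizumab item reads: "The administration of one or more doses of bevacizumab for presumed pseudoprogression, in cases with a final diagnosis of tumor progression". A further item covers chemotherapy started or altered for presumed progression when the final diagnosis is pseudoprogression. Scoring "will be done retrospectively, by the researchers and the treating physician after 6-month follow-up". Under Who will be blinded {17a}, nobody is.

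**Starting point of every patient.** Inclusion requires the "First moment of clinicoradiological uncertainty regarding the diagnosis". Background and rationale {6a} says that in current Dutch practice "the multidisciplinary team prefers to wait for a next scan".

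**The concern.** The surgery item joins two criteria with and/or: the reason for operating (diagnostic doubt) and the pathology result. Either is enough. The second makes no allowance for the indication, so it catches the operation that the intervention section itself names as appropriate. The endpoint is meant to capture harm from misdiagnosis, and in this patient there was none.

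The drug items have a related, less definite problem. They require treatment to be given on a presumption of pseudoprogression. Patients enter because the diagnosis is open, and an equivocal PET reading leaves it open. The text does not say whether carrying on with temozolomide, or giving bevacizumab, in that state counts as presuming pseudoprogression. As written, people who know the arm would settle it patient by patient, after the outcome is known.

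**Working it through.** **1. The surgery item applied to possible redo-debulkings**

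| Reason for surgery | Pathology | Scored? | Misdiagnosis or unresolved doubt drove it? |
|---|---|---|---|
| To settle the diagnosis | either | yes | yes |
| Presumed tumor | pseudoprogression | yes | yes |
| Refractory mass effect, pseudoprogression the working diagnosis | pseudoprogression | **yes** | **no** |
| Refractory mass effect, pseudoprogression the working diagnosis | tumor | no | no item applies to the surgery |

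The third row is the misclassification. It is the case in which pathology confirms the indication the protocol names. No other section provides an exception.

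**2. The plan's own figure**

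Inputs from Sample size {14}: 37% v 12%, two-sided alpha 0.05, power 90%, Z test with pooled variance.

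n per arm = [z(0.975)·√(2p̄q̄) + z(0.90)·√(p₁q₁ + p₂q₂)]² / (p₁ − p₂)², with p̄ = 0.245

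= [1.960 × 0.6082 + 1.2816 × 0.5820]² / 0.25² = 60.09, so **61 per arm**, as stated.

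Power at 72 per arm = Φ{[(p₁ − p₂) − 1.960·√(2p̄q̄/n)] / √[(p₁q₁ + p₂q₂)/n]}

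= Φ[(0.25 − 1.960 × 0.07168) / 0.06859] = Φ(1.597) = **0.945**.

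**3. How much the third row could matter**

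The documents give no rate for this surgery, so the points added are assumptions. They go to both arms because the event list is common to both.

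| Points added to each arm (assumed) | Patients per arm (of 72) | Rates | Power |
|---|---|---|---|
| 0 | 0 | 37% v 12% | 0.945 |
| 1 | 0.7 | 38% v 13% | 0.939 |
| 2 | 1.4 | 39% v 14% | 0.933 |
| 5 | 3.6 | 42% v 17% | 0.917 |

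**4. The drug items under an open diagnosis**

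- *Narrow reading.* The surgery item treats diagnostic uncertainty as a reason of its own, and the intervention section lists equivocal results separately from a PET diagnosis of pseudoprogression. Treatment given in doubt is then not given for presumed pseudoprogression and is not an event.
- *Broad reading.* The intervention section manages both readings alike, and the chemotherapy items recognize only two working positions: continue, or start or change. Continuing then amounts to acting on presumed pseudoprogression and is an event if the final diagnosis is progression.

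The broad reading is the more natural one, but the text does not exclude the narrow one. Sample size {14} does not say which one the survey behind the 37% used.

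**The case against.** **The two sections need not contradict each other.** One says what care may be given; the other says what is counted with hindsight. Care can be permitted and still be scored: treatment continued after a pseudoprogression reading is permitted, and it counts if progression proves to be the final diagnosis. This stands as a general point. It does not rescue the surgery item, because there hindsight confirms the working diagnosis and the operation is scored all the same. It does limit the claim: not every debulking of this kind is scored, only one whose pathology shows pseudoprogression.

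**It is rare and affects both arms.** This stands. A reader might infer that the surgery rule tilts the comparison for or against PET. The documents do not support that: the event list is common to both arms and no arm-specific frequency is given.

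**The drug wording is clear enough in context, and case rules may sit in the full protocol.** The first half largely stands, since the broad reading is the natural one. But the article sets out a definition of the primary endpoint, and the term that decides these cases is open.

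A reader might also infer a serious loss of power from the drug items. If rates planned on the broad reading were scored on the narrow one, assumed shares of 5 to 15 points in Arm B and 1 to 3 in Arm A would give 32% v 11% down to 22% v 9%, with power from 0.87 to 0.58. The documents do not support this. The shares are assumed. Their basis is patients with any such event, whereas the calculation needs patients with no other event. A mismatch between survey and assessors is not shown, and the reverse mismatch would raise power to 0.98 or more.

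**Conclusion.** The point holds in a limited form. The surgery item misclassifies an operation that the protocol itself indicates, and this follows from the wording without any assumption about rates. The numerical effect is probably small: planned power stays at or above 0.917 if up to 5 points are added to each arm, which is an assumed range. The case for correcting it is the validity of a primary event.

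The drug items carry a genuine but secondary ambiguity, worth closing because unblinded assessors would otherwise resolve it retrospectively. Its size cannot be stated from the documents, and neither a power loss nor a direction of bias is claimed.

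**What to change.** Amend the definition of co-primary outcome 1 in identical words for both arms, without looking at results by arm.

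1. **Surgery item.** Add: *Debulking for refractory symptoms of mass effect is not counted if the board notes before surgery record that indication and record pseudoprogression, or an unresolved diagnosis, as the working diagnosis, and if the operation was not done to settle the diagnosis.* Surgery for presumed tumor with pseudoprogression on pathology stays counted. Without the working-diagnosis condition, mass effect wrongly attributed to tumor would escape.

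2. **Temozolomide and bevacizumab items.** State that treatment given from randomization onward without a working diagnosis of progression counts if the final diagnosis is progression. Report the narrow reading as a sensitivity analysis, with the same rule in both arms, and state which reading the survey behind the 37% used.

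Do not use a trigger that differs by arm, such as an equivocal reading in Arm A and any recorded doubt in Arm B. All Arm B patients start in doubt, while that rule would miss Arm A cycles given before the PET result (about days 10–33, against randomization at about days 5–16) and Arm A patients never scanned, who remain in the intention-to-treat analysis. If both arms truly had 37% and such a rule added 3, 5 or 10 points to Arm B, the test at 72 per arm would reject in 0.066, 0.094 or 0.228 of trials.

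**Cost.** An amendment reported to the ethics committee and the registry; rescoring of patients already assessed (recruitment began in January 2025); and fields for surgical indication and working diagnosis, drawn from the multidisciplinary notes already listed under Other study parameters. The primary test and the sample size do not change.
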